##### Secondary Count Outcome for Aim 1: Emergency Department visits and Hospitalization visits during the 12 month Follow-up

**Hypothesis 1c:** We expect that adolescents who receive 10 days of sequential bilateral aTBS will have fewer emergency department visits and fewer hospitalization visits related to suicidality during the 12-months after the intervention compared to sham stimulation.

Emergency department visits and hospitalization visits related to suicidality will be assessed at monthly follow up visits over a 12-month period after the intervention. A separate Poisson

(or negative binomial) mixed model analysis will be used to estimate the number of emergency department visits and hospitalization visits, respectively, over the 12 months after intervention for those who received sequential bilateral aTBS vs. those who received sham stimulation. The model will contain fixed effects terms for treatment, time, treatment  $\times$  time interaction, and the same covariates identified in hypotheses 1a and 1b above. Simple treatment group effects in each time period will also be assessed. Maximum likelihood estimation, Type 3 tests of fixed effects, and generalized least squares means will be used along with the best fitting covariance structure. The sandwich (robust covariance matrix) estimator will also be considered. The Poisson model will be checked for overdispersion. The Poisson (or negative binomial) regression will model the logarithm of each outcome as a random variable, and the mean and variance will be estimated on the logarithmic scale. Thus, to facilitate interpretation, geometric means will be reported, which will be obtained by exponentiating the log-scaled parameter estimates. The procedures of PROC GLIMMIX in SAS software will be used to conduct the Poisson (or negative binomial) regression for Hypothesis 1c and provide a robust mechanism for handling data that are assumed missing at random (see sensitivity analysis section below for MNAR).

## Secondary Aim

### Data Analysis Plan for Secondary Aim 2 (Hypotheses 2a–2b)

#### Secondary Ordinal Outcome for Aim 2: Suicidal Ideation at Baseline Period

**Hypothesis 2a:** We expect that cortical inhibition (as assessed by pre-treatment LIC1-100 collected with TMS-EMG) will have an indirect relationship with severity of suicidal ideation (as assessed by the C-SSRS severity of ideation subscale) in all subjects at baseline.

An ordinal logistic regression model will be used to estimate severity of suicidal ideation at baseline from baseline measure of LIC1-100 collected with TMS-EMG. Age, sex, pubertal status, antidepressant medication status, and depression severity at baseline (CDRS-R total) will be included as covariates in the model. Maximum likelihood estimation and Type 3 tests of fixed effects will be used along with the Wald Chi-Square statistic. Robust standard errors (Huber Sandwich Estimator) will also be considered. For the ordinal logistic regression, the cumulative probabilities will be modeled over the lower-ordered suicidal ideation scale scores (less suicidal ideation). The adjusted odds ratios (i.e., odds of suicidal ideation from LIC1 with TMS-EMG), and 95% confidence interval, will be estimated as part of the model so as to interpret the relationship between the TMS-EMG biomarker and baseline suicidal ideation.

#### Secondary Ordinal Outcome for Aim 2: Suicidal Ideation during the 10-day acute Trial Period

**Hypothesis 2b:** We expect that, among the adolescents who receive active sequential bilateral aTBS treatment, there will be an indirect relationship between cortical inhibition (as assessed by LIC1-100 collected with TMS-EMG) and suicidal ideation (as assessed by the C-SSRS severity of ideation subscale) over the 10 day acute treatment trial.

An ordinal logistic regression model within a GEE analysis framework similar to that described above for Hypothesis 1a will be used here to examine the relationship between cortical inhibition (LIC1-100 collected with TMS-EMG as a time-varying covariate) and C-SSRS severity of ideation subscale (as the response variable) over the 10-day acute treatment trial. The parameter estimates (regression coefficients) will be interpreted from the solution for fixed effects in the GEE analysis. The adjusted odds ratio (i.e., odds of suicidal ideation from cortical

inhibition), and 95% confidence interval, will be estimated as part of the GEE model. The same covariates specified above in Hypothesis 1a will be included in the model for Hypothesis 2b.

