| Aims                                | 
Aim 1 examines the efficacy as assessed by the Columbia Suicide Severity Rating Scale (C-SSRS) severity of ideation subscale of sequential bilateral aTBS compared to sham stimulation over 10 days of active treatment and 12 months of follow-up. Aim 1 will also examine the impact of active vs sham sequential bilateral aTBS treatment on the number of emergency department visits and hospitalizations related to suicidality.
 
Aim 2 examines a biomarker of cortical inhibition called long interval cortical inhibition (LICI). It is expected that LICI will have an indirect relationship with severity of suicidal ideation as assessed with the C-SSRS severity of ideation subscale in all subjects at baseline. It is also expected that in adolescent subjects receiving active sequential bilateral aTBS treatment there will be an indirect relationship between LICI and the C-SSRS severity of ideation subscale over 10 days of treatment.
 
Exploratory aims focus on the development of TMS-EEG measures of cortical inhibition.
 |
| Number of Subjects                  | 80                                                                                                                                                                                                                                                                                                                                                                                                                                                                                                                                                                                                                                                                                                                                                                                                                                                                                                                                                                                                                                                                          |

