In preparation for study design our group reviewed current literature examining accelerated TMS protocols and published a meta-analysis (Figure 5). There was variability in published protocols. Summary analysis of three randomized controlled trials yielded an effect size (Hedges' *g*) of 0.4. Another analysis of all active arms and open-label studies revealed an effect size (Hedges' *g*) of 1.3. Preliminary results suggested that aTBS improved suicidal ideation in adults with MDD.

[figure not shown]

Figure 5. Prior studies of accelerated TMS

[figure not shown]

Figure 6. Indexing suicidal ideation with long-interval cortical Inhibition (LICI) biomarkers

that depressed adolescents with suicidal behaviour have impaired LICI and GABAB mediated inhibition compared to depressed adolescents with no history of suicidal behaviors and healthy controls. Please note that larger LICI values denote diminished inhibition (Figure 6). In another longitudinal study of suicidal adolescents in treatment for depression, enhancements in LICI measures correlated with improvements in suicidal ideation (assessed with the C-SSRS subscale for severity of suicidal ideation) after controlling for depression severity. Other recent work demonstrated the utility of TMS-EEG measures of LICI and N100 as target engagement biomarkers for brain stimulation interventions of suicidal ideation in adults with

The paired-pulse paradigm LICI provides an index of GABAB receptor mediated inhibition. A suprathreshold test stimulus is applied to the motor cortex eliciting a motor evoked potential (MEP) in the contralateral abductor pollicis brevis electrode. During LICI testing, suprathreshold conditioning and test stimuli are applied with interstimulus intervals (ISIs) of 100-200 ms which results in a MEP of diminished amplitude. This resultant inhibition is mediated by GABAB receptors. Our prior studies demonstrate

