## 2 Study Objectives

Suicide is a leading cause of death in adolescents worldwide. In the United States up to 18% of all teenagers seriously contemplate suicide each year. Few prior studies have focused on developing treatments for adolescents with active suicidal ideation. Outcomes related to suicidality in adolescents have not improved in recent decades. There is an urgent, unmet need for brain-based interventions and predictive biomarkers for suicidal ideation in adolescents.

To address these problems we will examine a transcranial magnetic stimulation (TMS) intervention and electrophysiological biomarkers. Accelerated TMS protocols delivered with theta burst stimulation (TBS) induce synaptic plasticity rapidly and overcome

practical limitations of TMS. Our prior work suggests that a standard cortical inhibition TMS electromyography (TMS-EMG) paradigm, long-interval intracortical inhibition (LICI) has utility in assessing suicidal ideation in adolescents. This LICI biomarker is easily collected in clinic. Transcranial Magnetic Stimulation-Electroencephalography (TMS-EEG) LICI and N100 measures may provide more direct measures of cortical inhibition in the prefrontal cortex but have not been adequately studied in adolescents with depression and suicidal ideation. The proposed, double-blind, randomized, sham-controlled study will examine sequential bilateral accelerated TBS (aTBS) for suicidal ideation in adolescents with major depressive disorder (MDD). All subjects (in both arms) will concurrently receive standard of care treatment. Three TBS sessions will be administered daily for 10 days (5 days per week) for a total of 30 sessions. During each session, continuous theta burst stimulation (cTBS) is first delivered to the right dorsolateral prefrontal cortex and then iTBS is delivered to the left dorsolateral prefrontal cortex. The proposed TBS parameters were adopted from prior work in adolescents. The comparison group will receive 3 daily sessions of bilateral sham TBS treatment for 10 days. The research team will collect pre- and post-treatment TMS-EMG LICI-100, TMS-EEG N45, and N100 biomarkers

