## 2.2 Secondary Objective

**Secondary Aim 2 examines TMS-EMG LICI as a predictive and target engagement biomarker for suicidality in adolescents with MDD.**

- **Hypothesis 2a:** We expect that cortical inhibition (as assessed by pre-treatment LICI-100 collected with TMS-EMG) will have an indirect relationship with severity of

suicidal ideation (as assessed by the C-SSRS severity of ideation subscale) in all subjects at baseline.

- **Hypothesis 2b:** We expect that, among the adolescents who receive active sequential bilateral aTBS treatment, there will be an indirect relationship between cortical inhibition (as assessed by LICI-100, TMS-EMG) and suicidal ideation (as assessed by the C-SSRS severity of ideation subscale) over the 10 day acute treatment trial.

**An exploratory Aim focuses on developing TMS-EEG measures of cortical inhibition (TMS-EEG N45 and N100) for assessing suicide risk and responsiveness to aTBS in adolescents with MDD.**

This is the first study to examine sequential, bilateral accelerated TBS in depressed adolescents with suicidal ideation. Sequential bilateral aTBS and the proposed panel of biomarkers will be rapidly implemented in the clinic. This novel approach will facilitate a critical paradigm shift toward brain-based approaches for assessing and treating suicidal ideation in adolescents with MDD.

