| YMRS-Young Mania Rating Scale                                                        | This is an 11-item measure used to assess for manic symptoms. The YMRS scale will be completed at baseline and repeated during the course of study participation if symptoms of mania occur in a study subject. If the YMRS is positive, A MINI/MINI-Kid will be repeated to evaluate for mania. If the study subject meets full DSM-5 criteria for mania or hypomania he or she will be discontinued from the study and followed clinically.                                                                                                                                                                                                                                                                                                                                                                                                                                                                                                                                                                                                |
| TMS Neurophysiology Measures                                                         | TMS-EMG (LICI-100) and TMS-EEG (LICI-100 and N100) neurophysiology measures will be collected in adolescent subjects at baseline and after the final day of sequential bilateral aTBS.
25, 81                                                                                                                                                                                                                                                                                                                                                                                                                                                                                                                                                                                                                                                                                                                                                                                                                                                           |

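### Hypothesis 2b cannot show target engagement: it relates LICI, measured twice, to ten daily ideation ratings within the active arm only

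*Protocol*

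**What the plan says.** **Purpose.** Protocol section 2.2 states that the secondary aim "examines TMS-EMG LICI as a predictive and target engagement biomarker for suicidality in adolescents with MDD". Section 3.3 repeats this.

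**Analysis.** Section 7.2 gives Aim 2 two hypotheses.
- Hypothesis 2a relates baseline LICI-100 to baseline C-SSRS ideation severity in all subjects.
- Hypothesis 2b covers the treatment period. It is restricted to an association "among the adolescents who receive active sequential bilateral aTBS treatment". Its model is a GEE like that of Hypothesis 1a, with the same covariates, and takes LICI-100 "collected with TMS-EMG as a time-varying covariate) and C-SSRS severity of ideation subscale (as the response variable) over the 10-day acute treatment trial".

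**Schedule.** Section 2 says "The research team will collect pre- and post-treatment TMS-EMG LICI-100, TMS-EEG N45, and N100 biomarkers". Table 4 in section 6.4 says that the "neurophysiology measures will be collected in adolescent subjects at baseline and after the final day of sequential bilateral aTBS". Table 3 marks the neurophysiology measures at baseline and posttreatment only, without distinguishing the arms. The C-SSRS is rated on each of the ten treatment days.

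**Direction.** Section 1.4 notes: "Please note that larger LICI values denote diminished inhibition". The Aims row of the Study Summary nevertheless says: "It is expected that LICI will have an indirect relationship with severity of suicidal ideation".

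**The concern.** Target engagement means that the stimulation changes the target. Hypothesis 2b asks something else: whether LICI and ideation go together in stimulated participants. If they go together in depressed adolescents generally, the test will tend to be positive whether or not aTBS does anything to cortical inhibition. The sham arm could separate the two explanations. It is scheduled for the same two LICI measurements, but no planned analysis uses its posttreatment value.

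The model also does not fit the data that it will receive. A covariate observed twice is asked to track ten daily ratings. The treatment and treatment-by-time terms of the Hypothesis 1a model have no meaning in a single-arm analysis.

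Section 2.1 presents this as a pilot for pivotal studies, and section 2.2 foresees rapid clinical use of the biomarker panel. A positive Hypothesis 2b could therefore be carried forward as evidence of mechanism that the analysis does not supply.

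**Working it through.** **1. The sample available.** Section 7.1 sizes the trial for Hypothesis 1a only. Its inputs are sham proportion 0.50, odds ratio 2.85, ten repeated measures, within-subject correlation 0.50, two-sided 0.05 and 80% power.
- Active proportion: 2.85 / 3.85 = 0.740.
- Pooled two-proportion formula: n = [1.960 × √(2 × 0.620 × 0.380) + 0.842 × √(0.250 + 0.192)]² / 0.240² ≈ 63 per group.
- Repeated-measures factor: (1 + 9 × 0.50) / 10 = 0.55.
- 63 × 0.55 = 34.65, rounded up to 35 per group. Power at 35 is 0.805.
- Dropout: 70 / 0.90 = 77.8, consistent with about 80 enrolled.

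The plan's figure of 35 per group reproduces. It is used below as the number with LICI at both visits.

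**2. LICI values against daily ratings.** Each participant has two LICI-100 values and ten daily C-SSRS ratings.
- The posttreatment value goes with the end-of-treatment rating.
- The baseline value may also go with a response row. Section 6.2 places baseline neurophysiology and the first treatment day in the same visit, but does not say whether the day-1 C-SSRS is separate from the baseline rating. Baseline C-SSRS is itself a covariate.
- So one or two of the ten ratings have a LICI value from the same visit, and eight or nine do not. For 35 active participants that is 35 to 70 matched rows out of 350.
- Carrying the baseline value forward would hold LICI constant until the end. Its only within-person change would then coincide with the end of treatment.

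**3. Terms that drop out.** The Hypothesis 1a model contains treatment, time and treatment by time. With active participants only, the first and third cannot be estimated.

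**4. What a positive Hypothesis 2b would mean.** A simulation of 4,000 trials used 35 per arm, no treatment effect on LICI change, and LICI change correlated with ideation change equally in both arms. The correlation r is an assumption, because the documents give none. A simple correlation test stands in for the ordinal GEE. Share of trials significant at 0.05:

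| Assumed r | Active-only association | Sham-only association | LICI change, active vs sham |
|---|---|---|---|
| 0 | 5.8% | 5.1% | 4.8% |
| 0.3 | 43% | 42% | 4.6% |
| 0.5 | 90% | 89% | 4.8% |

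The active-only test responds to the association, which is equally present under sham. Only the between-arm comparison keeps its error rate when aTBS does nothing to LICI.

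**5. What the repaired analyses could detect.** The protocol gives no SD for LICI, so results are in SD units.
- LICI change between arms, 35 per arm: d = (1.960 + 0.842) × √(2/35) = 0.67 for 80% power. Power is 0.24 at d = 0.3, 0.55 at d = 0.5 and 0.92 at d = 0.8.
- Association, from r = tanh[(1.960 + 0.842) / √(n − 3)]: n = 35 gives 0.46 and n = 70 gives 0.33.

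**6. Direction.** Section 6.4 expresses LICI as conditioned MEP amplitude in percent of unconditioned amplitude, so a higher value is less inhibition. An inverse relation between inhibition and ideation, as in Hypotheses 2a and 2b, is therefore a positive relation between the LICI value and ideation. The Summary states the inverse relation for LICI itself.

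**The case against.** **Sparse covariates are a matter for the SAP.** CDRS-R is also entered as time-varying in the ten-day model, although it is collected only at baseline, after five treatments and at posttreatment. A two-point covariate is technically time-varying. How it maps to daily rows is commonly left to the SAP, which is not shown. This stands in part: the missing alignment rule is no finding in itself. But no rule gives two values the information of a ten-day course, and the single-arm population is fixed in the protocol.

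**The model adjusts for background change.** With two or more rows per participant, the time term absorbs average change from psychotherapy or regression to the mean. This stands. What it does not absorb is correlated individual change, which the simulation isolates.

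**Stronger readings that the documents do not support.**
- A reader might infer that only one row per participant is usable and that nine of ten ratings contribute nothing. Section 6.2 leaves open a matched day-1 row, and the protocol does not state that unmatched rows are deleted.
- A reader might take the word predictive to require a baseline LICI-by-treatment interaction. Sections 1.1 and 1.4 describe the baseline role as indexing ideation severity, which Hypothesis 2a addresses.
- A reader might conclude that the hypotheses carry the wrong sign. Section 2.2 and Hypotheses 2a and 2b are worded on cortical inhibition and agree with section 1.4. Only the Summary's shorthand is loose.

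**Conclusion.** The point holds as a should-fix. Aim 2 claims target engagement, but the planned treatment-period test is a one-arm association. It could be positive in a large share of trials with no aTBS effect on LICI: 43% and 90% under assumed correlations of 0.3 and 0.5. These percentages depend on the assumed correlation and on a simplified test. The conclusion that an active-only association cannot separate a stimulation effect from a general association depends on neither.

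The mismatch between two LICI measurements and ten ratings is secondary but real: eight or nine of the ten ratings have no LICI value from the same visit.

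The limit lies in the planned analyses. The scheduled data can support the aim. Hypothesis 1a and its sample size are untouched. Hypothesis 3b has the same two faults for the TMS-EEG measures.

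**What to change.** Before unblinding, amend section 7.2 as follows.

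1. **Target engagement.** Add a both-arm analysis of posttreatment LICI-100 by randomized arm, adjusted for baseline LICI-100.
2. **Association.** Replace the ten-day model of Hypothesis 2b with an ordinal model at the measured timepoints: posttreatment C-SSRS ideation severity on change in LICI-100, adjusted for baseline C-SSRS, in both arms with a term for arm.
3. **Hypothesis 3b.** Make the same two changes for the TMS-EEG measures.
4. **Wording.** State the Summary hypothesis on the measured value: a higher LICI ratio, meaning less inhibition, goes with more severe ideation.

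A baseline LICI-by-treatment test may be added as exploratory, but the aim as described does not require it.

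**Cost.** No new measurements are needed. There are one or two extra secondary tests for Aim 2 under the False Discovery Rate adjustment. Power for the arm comparison is modest, about d = 0.67 at 35 per arm, so a null result should be reported with its confidence interval and not as absence of engagement.

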## **Exploratory Aim**

### **Data Analysis Plan for Exploratory Aim 3 (Hypotheses 3a–3b)**

#### Exploratory Ordinal Outcome for Aim 3: Suicidal Ideation at Baseline Period

**Hypothesis 3a:** We expect that cortical inhibition (as assessed by pre-treatment LIC1-100 and N100 collected with TMS-EEG) will have an indirect relationship with severity of suicidal ideation (as assessed by the C-SSRS severity of ideation subscale) in all participants at baseline.

An ordinal logistic regression model similar to that described above for Hypothesis 2a will be used to estimate severity of suicidal ideation at baseline from baseline measures of LIC1-100 and N100. A separate model will be implemented for each measure of TMS-EEG cortical inhibition. The same covariates specified in Hypothesis 2a will be included in the model for Hypothesis 3a. The adjusted odds ratios (i.e., odds of suicidal ideation from LIC1-100 and N100), and 95% confidence interval, will be estimated as part of the model so as to interpret the relationship between each TMS-EEG biomarker and baseline suicidal ideation.

